## 8. ADVERSE EVENT REPORTING

The collection and reporting of Adverse Events (AEs) will be in accordance with the Medicines for Human Use Clinical Trials Regulations 2004 and its subsequent amendments. Definitions of different types of AE are listed in Appendix 3. The Investigator should assess the seriousness and causality (relatedness) of all AEs experienced by the patient (this should be documented in the source data) with reference to the SPC.

### 8.1 Reporting Requirements

#### 8.1.1 Adverse Events

All medical occurrences which meet the definition of an AE (see Appendix 3 for definition) should be reported. Please note this does not include abnormal laboratory findings. An abnormal laboratory value is only considered to be an AE if the abnormality:

- Results in early discontinuation from the study treatment and/or
- Requires study drug dose modification or interruption, any other therapeutic intervention or is judged to be of significant clinical importance

If a laboratory abnormality is one component of a diagnosis or syndrome, then only the diagnosis or syndrome should be recorded.

Pre-existing symptoms present prior to commencing trial treatment should only be reported as an AE if they increase in grade.

Details of all AEs experienced by the patient should be recorded in the hospital notes.

AEs should be graded according to Common Terminology Criteria for Adverse Events (CTCAE) v4.0 criteria and relatedness to the study IMP should be assessed by the Investigator. All AEs should be recorded via the running Adverse Events Form throughout the study. Where the patient experiences a change in grade of an AE, each change in grade should be recorded as a new AE.

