### 7.9 Patient Withdrawal

In the event of discontinuation of study treatment, e.g. unacceptable toxicity or patient choice, full details of the reason/s for discontinuation should be recorded on the CRF.

All patients, including non-compliant subjects, should be followed up according to the protocol schedule unless they withdraw specific consent.

In the event of a patient's decision to withdraw from the trial, the Investigator should ascertain from which aspects of the trial the patient wishes to withdraw and record the details on the appropriate CRF. All information and blood/bone marrow samples collected up until the point of retraction will be retained and analysed. If a patient chooses to withdraw from treatment only, the patient should discontinue treatment and continue to be assessed in accordance with the protocol. If a patient wishes to withdraw from the trial (i.e. including trial specific assessments), but is willing for further data to be supplied to the Trials Office, then further routine 'follow-up' data (e.g. toxicity data) will continue to be supplied by the Investigator to the Trials Office.

Patients who stop treatment due to adverse experiences (clinical or laboratory) will be treated and followed according to accepted medical practice. All pertinent information concerning the outcome of such treatment must be recorded in the CRF.

The following are justifiable reasons for the Investigator to stop study treatment:

- Unforeseen events: any event which in the judgement of the Investigator makes further treatment inadvisable
- Serious violation of the trial protocol (including persistent patient non-attendance and persistent non-compliance)
- Stopping by the Investigator for clinical reasons not related to the study drug treatment

Patients must stop study treatment in the event of:

- Unacceptable toxicity, defined as:
  - Grade 3-4 adverse event considered related to the trial IMP
  - Persisting grade 1-2 adverse events considered related to the trial IMP lasting more than 14 days and that do not resolve within 4 weeks of reducing tamoxifen to 10 mg od
- Thrombotic event of any grade
- SAE requiring permanent discontinuation of treatment
- Transformation to MDS or AML

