### 10.3 Central Monitoring

Where a patient has given explicit consent sites are requested to send in copies of signed Informed Consent Forms for in-house review.

Trials staff will be in regular contact with the site research team to check on progress and address any queries that they may have. Trials staff will check completed CRFs for compliance with the protocol, data consistency, missing data and timing. Sites will be sent Data Clarification Forms via the eRDC system requesting missing data or clarification of inconsistencies or discrepancies.

Sites may be suspended from further recruitment in the event of serious and persistent non-compliance with the protocol and/or GCP, and/or poor recruitment. Any major problems identified during monitoring may be reported to Trial Management Group (TMG) and Trial Steering Committee (TSC) and the relevant regulatory bodies. This includes reporting serious breaches of GCP and/or the trial protocol to the main REC) and the MHRA.

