#### 12.1.2 Secondary outcome measures

- Proportion of patients with a reduction in the peripheral blood JAK2-V617F, CALR 5bp insertion (exon 9), or CALR 52bp deletion (exon 9) mutant allele burden of  $\geq 50\%$  at 12 weeks
- Toxicity measured as the number of grade 3 and 4 adverse events reported.
- The number of thrombotic events of any grade reported and validated.
- Haematological response, assessed at weeks 12 and 24, for patients who enter the study in response (CR or PR). Haematological response is defined according to 2009 ELN criteria for ET/PV patients and no evidence of disease progression for MF patients according to IWG-MRT response criteria (for criteria see Appendices 5 & 6).
- Proportion of patients in each response category according to IWG-MRT response criteria for MF patients and 2013 ELN response criteria for ET/PV patients at 24 weeks of treatment.
- Proportion of patients showing an improvement in response category at 24 weeks compared to baseline according to 2009 ELN criteria for ET/PV patients [1] and according to IWG-MRT response criteria [2] for MF patients. Patients who are in a higher category at week 24 compared to baseline will be classed a success. Patients who enter the trial in CR and who maintain a CR will also be classed as a success in this outcome.

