### 12.2.2 Secondary outcome measures

All secondary outcomes will be analysed in a descriptive manner on an intention to treat basis with no formal hypothesis testing taking place.

- The reduction in the allele burden of  $\geq 50\%$  at 12 weeks will also be obtained following analysis of peripheral blood at University of Cambridge. Counts and percentages of patients who have achieved each level of reduction at 12 weeks will be presented. Patients who die or are lost to follow up prior to 12 weeks will be classed as non-responders.
- The total number of grade 3 and 4 adverse events reported will be presented as well as the number of patients who have experienced one or more of these events.
- The total number of thrombotic events (of all grades) will be reported as well as the number of patients who have experienced one or more of these events.
- Haematological response at weeks 12 and 24 will be tabulated and compared using a  $\chi^2$  test or Fisher's exact test if the first is not considered appropriate.
- Proportion of patients in each response category at 24 weeks of treatment will be presented as the number and percentage of patients in each category.
- Proportion of patients showing an improvement in response category at 24 weeks will be presented as the number and percentage of patients who have shown an improvement (or maintained a CR).

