### 12.4 Planned Interim Analysis

Accumulating data will be analysed and presented on a regular basis (6 monthly) to an independent TSC for monitoring of safety and futility. Analysis will also be performed and presented to the TSC if 7 or more patients out of the first 21 patients registered are deemed to not have tolerated treatment. A patient is classed as not being able to tolerate treatment if they discontinue treatment due to:

- Unacceptable toxicity, defined as:
  - Grade 3-4 adverse event considered related to tamoxifen
  - Persisting grade 1-2 adverse events considered related to tamoxifen lasting more than 14 days and that do not resolve within 4 weeks of reducing tamoxifen to 10 mg od
- Thrombotic event of any grade

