### 13.4 Trial Steering Committee

Data analyses will be supplied in confidence to an independent TSC which will be asked to give advice on whether the accumulated data from the trial, together with the results from other relevant research, justifies the continuing recruitment of further patients. During the recruitment phase of the trial the TSC is scheduled to meet 6 monthly. Additional meetings may be called if recruitment is much faster than anticipated and the TSC may, at their discretion, request to meet more frequently or continue to meet following completion of recruitment. An emergency meeting may also be convened if a safety issue is identified. The TSC would also be convened to monitor the safety of the trial in mind of the efficacy if 7 out of the first 21 patients registered to the trial do not tolerate treatment. See section 12.4.

The TSC will report directly to the Trial Management Group (TMG) who will convey the findings to the Sponsor, MHRA, REC or funder if applicable. The TSC may consider recommending the discontinuation of the trial if the recruitment rate or data quality are unacceptable or if any issues are identified which may compromise patient safety.

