## APPENDIX 3 - DEFINITION OF ADVERSE EVENTS

### Adverse Event

Any untoward medical occurrence in a patient or clinical trial subject administered a medicinal product and which does not necessarily have a causal relationship with this treatment.

Comment:

An AE can therefore be any unfavourable and unintended sign, symptom or disease temporally associated with the use of an investigational medicinal product, whether or not related to the investigational medicinal product.

Please note this does not include abnormal laboratory findings. An abnormal laboratory value is only considered to be an AE if the abnormality:

- Results in early discontinuation from the study treatment and/or
- Requires study drug dose modification or interruption, any other therapeutic intervention or is judged to be of significant clinical importance

If a laboratory abnormality is one component of a diagnosis or syndrome, then only the diagnosis or syndrome should be recorded.

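### The grade 3-4 toxicity outcome leaves out laboratory values that were neither acted on nor judged important, and section 12 plans no graded laboratory table beside it

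*Combined protocol and SAP*

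**What the plan says.** **Adverse event definition.** Section 8.1.1 and Appendix 3 give the same rule. The default is exclusion: "Please note this does not include abnormal laboratory findings". The exception follows: "An abnormal laboratory value is only considered to be an AE if the abnormality" ends study treatment early, leads to a tamoxifen dose change or pause, needs another treatment, or is judged clinically important. The text does not say who judges importance; the natural reading is the site.

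**Toxicity outcome.** Section 12.1.2 has "Toxicity measured as the number of grade 3 and 4 adverse events reported". Section 12.2.2 has "The total number of grade 3 and 4 adverse events reported will be presented", together with the number of patients who have at least one.

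**Laboratory data.** Haematology and biochemistry are scheduled at baseline, weeks 4, 12, 18 and 24, and 28 days after stopping (7.2.4, 7.2.5). Fasting lipids are measured at baseline, week 12 and week 24 (7.2.6). The CRF forms in 9.1 record haematology and biochemistry. That list is stated to be incomplete and does not name lipids.

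**Oversight.** Under 10.3, "Trials staff will check completed CRFs for compliance with the protocol, data consistency, missing data and timing". Under 13.4, "Data analyses will be supplied in confidence to an independent TSC". Neither 12.4 nor 13.4 lists what the TSC reports contain.

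**The concern.** Safety is a stated aim (2.1), and section 1.2.2 gives the lack of experience with tamoxifen in this disease, and alongside cytoreductive drugs, as the reason for monitoring toxicity. Cytoreduction continues during the trial (7.6), and 7.2.6 itself links tamoxifen to raised triglycerides. Laboratory toxicity is therefore a foreseeable question.

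As planned, the only graded toxicity result passes through a filter of action or clinical judgement before anything is counted. Two patients with the same grade 3-4 value can be counted differently if one team judges it important and another does not. A reader of the final report who sees few grade 3-4 events could not tell whether few severe laboratory values occurred or whether some occurred and were not classed as events.

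**Working it through.** **Inputs.** Planned sample 42 (12.6); 13 to 15 centres (Trial Duration in the synopsis). The documents give no rate of laboratory toxicity.

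**The denominator.** The planned 42 reproduces. With 3 or more responders required, the exact binomial tail for n = 42 is 0.0515 at a 2% response rate (limit 0.10) and 0.8049 at 10% (target 80%). No smaller sample meets both limits. The present point does not depend on this calculation and uses 42 only as a denominator.

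**Tracing one value through the plan.** Take a new grade 3-4 value that led to no action and was not judged important.
1. Under 8.1.1 and Appendix 3 it is not an adverse event, whatever its grade.
2. It therefore cannot enter the count in 12.1.2 and 12.2.2.
3. Nothing else in section 12 picks it up as a safety result. The other safety items are thrombotic events and the TSC review. Some blood counts feed the haematological response outcomes, but as response criteria. Appendix 6 uses a two-grade fall in platelets or neutrophils, but only to define clinical improvement in myelofibrosis.
4. Central monitoring (10.3) sets no laboratory threshold, and leaving this value unreported complies with the protocol.
5. The TSC reports may or may not show it, because their content is not specified.

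**Size per patient.** Each patient left out who has no other reported grade 3-4 event changes the reported proportion by 1/42 = 0.024, or 2.4 percentage points.

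**Spread of the judgement.** 42/15 = 2.8 and 42/13 = 3.2, so on average each centre makes this judgement for about 3 patients.

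**Illustration only.** These rates are assumptions, not figures from the documents. If a fraction p of patients had such a value, the expected number left out is 42p, and the chance of at least one is 1 − (1 − p)^42.

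| Assumed p | Expected patients left out | Chance of at least one |
|---|---|---|
| 0% | 0 | 0% |
| 2% | 0.8 | 57% |
| 5% | 2.1 | 88% |
| 10% | 4.2 | 99% |

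**Why baseline grade is needed.** Section 4 sets upper limits for platelets and white cells in PV and ET but no lower limit for haemoglobin, neutrophils or platelets. A patient can enter with a low count, so a worst grade alone would not show what is new on treatment.

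**The case against.** The definition is deliberate and consistent: 8.1.1 and Appendix 3 agree, and 12.2.2 analyses exactly what 12.1.2 defines. The gap is narrow, because any value that led to a transfusion, lipid treatment, dose change or discontinuation is already an adverse event. Tamoxifen dose changes also go through the Chief Investigator or Clinical Coordinator (7.4), so those are seen centrally. Investigator judgement enters all adverse event reporting. Since most of the values are on the CRF, a table could be produced at reporting without being planned. All of this stands. It limits the importance of the point but does not put the omitted values back into any stated analysis. A table specified in advance is also more credible than one chosen after the data are seen.

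A reader might go further and infer that the safety rules are compromised, because the stop in 7.9 applies to a "Grade 3-4 adverse event considered related to the trial IMP" and the 12.4 review is called "if 7 or more patients out of the first 21 patients registered are deemed to not have tolerated treatment". The documents do not support that. The trigger counts patients who discontinue, and any laboratory value that leads to discontinuation is an adverse event by the first condition in 8.1.1. For grade 3-4 events, both rules also require relatedness to tamoxifen. A patient who was not stopped is not intolerant as 12.4 defines it.

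A reader might also infer that the trial will understate toxicity. That is not shown either: no rate is given, and the number of patients left out may be zero.

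**Conclusion.** The point holds as a gap in reporting. On the text of 8.1.1, Appendix 3, 12.1.2 and 12.2.2, a grade 3-4 laboratory value that was neither acted on nor judged important is absent from the toxicity outcome, and section 12 plans no other graded account of laboratory safety. The effect is 2.4 percentage points per affected patient, for an unknown number that may be zero. The outcome is secondary and descriptive, so the sample size, error rates and primary decision are untouched.

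Two assumptions matter. The first is that importance is judged at the site, which the text implies but does not say. The second is that the TSC reports do not already carry graded laboratory values, which the documents leave open. If they do, the TSC part of the fix is already met and only the final analysis needs the addition.

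**What to change.** Keep the adverse event definition. In 12.2.2, and in the 6-monthly TSC safety reports if it is not already there, add a descriptive table derived centrally:

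- worst on-treatment CTCAE v4.0 grade for each laboratory parameter, with shift from baseline grade;
- haematology and biochemistry values already on the CRF, plus triglycerides at baseline, week 12 and week 24 once their capture on the CRF is confirmed;
- the number of patients with a new grade 3-4 laboratory value, shown beside the reported grade 3-4 adverse events.

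State that an entry in this table does not by itself count under 7.9 or towards the 7-of-21 trigger. I would not add a routine query for each such value. A query could turn a value nobody acted on into a related grade 3-4 event that mandates stopping under 7.9, and an early stop can put the week 24 allele burden sample outside the window in 7.8.

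**Cost.** Some programming, and possibly one lipid field, which 9.1 allows without a protocol amendment. The 12.2.2 wording can go in with the next amendment. The table will have gaps where week 18 is done by telephone without blood tests. With one arm and continuing cytoreduction it cannot attribute a change to tamoxifen. The safety profile may look less favourable than the event count alone.

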## 3. TRIAL DESIGN

This is a single arm, open label, multicentre, phase II trial of tamoxifen in patients with MPNs.

The aim of the study is to evaluate the activity of tamoxifen in terms of reducing allele burden and the safety of giving tamoxifen in this group of patients. A single stage A'herns design has been chosen to give evidence of activity for the treatment.

All patients will receive a minimum of 24 weeks of treatment with tamoxifen at 20mg od. Patients will be seen at weeks 4, 12, 18 and 24. Mutant allele burden of JAK2-V617F, CALR 5bp insertion (exon 9) and CALR 52bp deletion (exon 9) will be assessed at baseline. Allele burden will be reassessed at 12 weeks and 24 weeks for the mutation(s) identified at baseline. Patients may continue treatment

beyond 24 weeks at the discretion of the treating Investigator. If patients do continue treatment they should be followed up a minimum of 12 weekly and their allele burden reassessed at 36 weeks and 48 weeks as applicable. All patients will be followed up until 28 days after the last dose of tamoxifen treatment.

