## 8.2 Reporting Procedure

### 8.2.1 Site

#### 8.2.1.1 Adverse Events

AEs should be reported on an AE Form (and where applicable on an SAE Form). The AE Form is a continuous form completed via the eCRF. The form should be checked and updated as applicable at each visit.

AEs will be reviewed using the CTCAE version 4.0 (see Appendix 4). Any AEs experienced by the patient but not included in the CTCAE should be graded by an Investigator and recorded on the AE Form using a scale of (1) mild, (2) moderate or (3) severe. For each sign/symptom, the highest grade observed since the last visit should be recorded.

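### The total of grade 3-4 adverse events has no defined counting unit: sections 8.1.1 and 8.2.1.1 give different recording rules for the same form, and the total depends on which one a site follows

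*Combined protocol and SAP*

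**What the plan says.** Two parts of section 8 tell sites how to record a change in severity.

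- Section 8.1.1: "All AEs should be recorded via the running Adverse Events Form throughout the study", followed by "Where the patient experiences a change in grade of an AE, each change in grade should be recorded as a new AE".
- Section 8.2.1.1: "The AE Form is a continuous form completed via the eCRF", to be checked and updated at each visit, and "For each sign/symptom, the highest grade observed since the last visit should be recorded".

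Both describe the same continuous form, and neither says which rule takes precedence.

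The statistical section then uses the records. Section 12.1.2 defines the outcome as "Toxicity measured as the number of grade 3 and 4 adverse events reported"; the synopsis and section 2.2 agree. Section 12.2.2 plans the event total: "The total number of grade 3 and 4 adverse events reported will be presented". Beside it, the section plans a patient-level count of those with at least one such event. It gives no rule for merging records that belong to one episode. All secondary outcomes are descriptive, without formal testing.

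**The concern.** A count of events needs a unit. If each change in grade is a new event, the unit is a stretch of constant grade. If the worst grade since the last visit is what gets recorded, the unit is a visit interval. Neither is a toxic episode, which is how a reader would take the reported number.

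A site cannot satisfy both sentences literally when a grade changes between visits: one asks for every step, the other only for the peak. Two sites with identical patients could therefore contribute different numbers to the same total. Safety is the trial's second stated aim (section 2.1), and the event count is the only measure named in the definition of the toxicity outcome.

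**Working it through.** The plan states no figure to reproduce here. The check is to apply each rule to the same courses and count the grade 3-4 records. The courses are illustrations, not trial data.

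**Inputs**

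- Rule A (section 8.1.1): a new record at each change in grade.
- Rule B (section 8.2.1.1): one record per sign or symptom per visit interval, at the highest grade. This takes it literally, with an entry at every visit while the event continues.
- Intervals (section 3): "Patients will be seen at weeks 4, 12, 18 and 24". Their lengths are 4, 12 − 4 = 8, 18 − 12 = 6 and 24 − 18 = 6 weeks, so a whole episode can fit inside one.

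**Formulas, for one episode**

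- A = number of stretches of constant grade in which the grade is 3 or 4.
- B = number of visit intervals in which the highest grade is 3 or 4.
- E = 1 if the worst grade is 3 or 4, otherwise 0 (one event per episode).

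**Results** (a bar marks a visit; with no bar, the course lies within one interval)

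| Course of one episode | A (8.1.1) | B (8.2.1.1) | E |
|---|---|---|---|
| 3 | 1 | 1 | 1 |
| 2-3-2 | 1 | 1 | 1 |
| 3-4 | 2 | 1 | 1 |
| 3-2-3 | 2 | 1 | 1 |
| 3-4-3 | 3 | 1 | 1 |
| 2-3-4-3-2 | 3 | 1 | 1 |
| 3-4 \| 3 | 3 | 2 | 1 |
| 3 \| 3 (unchanged) | 1 | 2 | 1 |

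For example, 2-3-4-3-2 has five stretches, of which the three at grades 3, 4 and 3 count, so A = 3. Its single interval peaks at grade 4, so B = 1.

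Three things follow.

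1. Rule A over-counts only when an episode has more than one stretch at grade 3-4. A rise to grade 3 and back counts once, because its grade 2 records fall outside the outcome.
2. Rule B can over-count too, when an event persists across a visit. In the last row B exceeds A, so neither rule always gives the larger total.
3. The patient-level count is the same under both rules. A patient whose worst grade is 3 or 4 has at least one such stretch and at least one such interval; a patient whose worst grade is lower has neither.

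**What else could be touched.** The trigger in section 12.4 counts patients who stop treatment for defined reasons (7 or more of the first 21), not event records. The primary outcome is allele burden. Neither uses the event total.

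**The case against.** The strongest reply is that the two sentences can be read together: section 8.2.1.1 sets what is observed (the worst grade in the interval), and section 8.1.1 opens a new line only when that value differs from the previous one. Then 3-4-3 within one interval gives one record, and an unchanged grade 3 event gives one record however many visits it spans. This is a reasonable reading, but the protocol does not state it. Nor does it fully repair the count: 3-4 | 3 has interval maxima 4 and 3, which differ, so one episode still yields 2 grade 3-4 records. The data-entry completion guidelines mentioned in section 9.1 may settle the matter, but they are not among the documents.

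The second reply is that little depends on the total. Section 12.2.2 already plans the patient-level count, the analysis is descriptive, there is no control arm, and section 8.1.1 leaves out most laboratory abnormalities, one likely source of fluctuating grades. All of this stands, and it limits the importance of the point. It does not supply a unit for the number that the outcome definition names.

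A reader might infer more than the documents support in three ways.

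- *That the total is inflated.* The last row of the table runs the other way, and a 2-3-2 course is counted correctly under both rules.
- *That the error can be given as a percentage.* The documents contain nothing on how often grades change within an episode.
- *That the thrombosis total has the same fault.* Thrombotic events are to be validated (section 12.1.2) and have their own Event Form, due after the event resolves (section 9.1). Nothing says they are counted from lines on the adverse event form.

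**Conclusion.** The point holds, with modest weight. Sections 8.1.1 and 8.2.1.1 give different recording rules for one form, and the toxicity outcome counts the resulting records with no rule for combining them. Followed literally, 8.1.1 counts a single 3-4 or 3-2-3 episode twice and a 3-4-3 episode three times. Followed literally, 8.2.1.1 may count an unchanged grade 3 event twice when it spans two intervals.

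The effect is confined to the descriptive total of grade 3-4 events. The number of patients with at least one such event, the 7-of-21 trigger and the primary outcome do not change. How far the total would move in this trial cannot be stated. The conclusion assumes that the event total is taken directly from the form's records, which is the plain sense of sections 12.1.2 and 12.2.2.

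**What to change.** Two changes.

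1. Reconcile sections 8.1.1 and 8.2.1.1 into one recording rule. Whichever is kept, the record needs a start date and a resolution date for each event.
2. State the counting unit in sections 12.1.2 and 12.2.2, for example:

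> *Records of the same CTCAE term in the same patient that follow one another without resolution in between are counted as one event, at the worst grade reached. Episodes separated by resolution are counted separately.*

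Report this total beside the patient-level count already planned. The condition on resolution matters: merging on the term alone would collapse separate episodes into one.

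The cost is one reconciled instruction in section 8, a sentence in section 12 and a short merge step in the adverse event program. No new visits or assessments are needed. The merge relies on start and resolution dates being captured. That is an assumption, because section 9.1 describes the form only in general terms and does not list its fields.
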